## Abstract

**Background:**

Regarding the paucity of evidence on the side effects of the booster dose of Oxford AstraZeneca vaccine in vaccinated people with Sinopharm or Sputnik V, we aimed to set up a cohort event monitoring (CEM) study to capture adverse events occurring in individuals who will receive the booster doses of AstraZeneca (either the first or second booster dose) following being vaccinated with Sinopharm or sputnik V vaccines in Iran.

**Methods:**

The present study is an active COVID-19 vaccine safety surveillance through an observational prospective cohort study that will be conducted in vaccination centers in Iran. The study will be conducted in twelve provinces of Iran. Study sites are vaccination centers where the AstraZeneca vaccine is administered to the cohort population. The study population includes all individuals who have received two doses of Sinopharm or Sputnik V vaccines and either the first or second booster dose of AstraZeneca according to the national guidelines for immunization in Iran in 2023. We are planning to include 30,000 eligible people in this study. Each individual will be followed up for 13 weeks after either the first or second booster dose of the AstraZeneca vaccine. Furthermore, convenience sampling is used to include participants in the present study. Participation in the study will be strictly voluntary.

**Discussion:**

With the planned study we will provide a valid epidemiological evidence to improve the understanding of the safety of the booster dose of the AstraZeneca and to better evaluate the effectiveness of public health interventions. This could help policy makers in managing the COVID-19 pandemic according to scientific evidence.

**Supplementary Information:**

The online version contains supplementary material available at 10.1186/s12889-023-16265-8.

## Background

In December 2019, an outbreak of respiratory disease caused by a novel coronavirus strain was reported in Wuhan City, Hubei Province, China. The novel coronavirus was named ‘severe acute respiratory syndrome coronavirus 2’ (SARS-CoV-2), while the disease associated with it is referred to as COVID-19. The virus quickly spread to different parts of China and other countries in the world [1].

The development of safe and effective vaccines is a vital approach to control of the SARS-CoV-2 pandemic. Providing equitable access to vaccines across the world is one of the critical approaches to mitigating the public health and economic impact of the pandemic [2]. Regarding the literature, vaccine candidates against COVID-19 comprise traditional virus- and protein-based vaccines and newer platforms like mRNA vaccines, viral vector-based- and nucleic acid vaccines [3]. Vaccines confirmed for use in national immunization programs (NIPs), are considered safe and effective based on verifiable evidence from randomized controlled clinical trials. However, studies indicate that vaccines are not entirely free of risks, despite rigorous safety evaluation during clinical development, and occasional adverse events will take place after vaccination at the population level [4–6]. Regarding that vaccines are often suggested for otherwise healthy individuals, the key to the success of NIPs will be public trust in vaccine safety [7].

Therefore, systematic vaccine safety surveillance is necessary for approving the safety of vaccines and public trust, across the world. When plans for immunization with COVID-19 vaccines are set up, there should be a pharmacovigilance systems simultaneously, and implement specific COVID-19 vaccine safety surveillance. In fact, WHO developed such protocol for COVID-19 vaccine safety surveillance manual [8]. Given that routine passive reporting systems might not be adequate to allow quick assessment and appropriate public health response during COVID-19 vaccine introduction; active safety surveillance is recommended.

In Iran, public vaccination with COVID-19 vaccines as part of the NIP was started in 2021. In addition to vaccines such as Sinopharm, Oxford/AstraZeneca ChAdOx1 nCoV-19 adenoviral AstraZeneca, and Sputnik V, Iranian received different types of domestic vaccines. Accruing to the Ministry of Health and Medical Education’s (MOHME) report on COVID-19 on August 16, 2022, the total number of cases, deaths, and recovered cases was 7,488,493; 143,093; and 7,190,330 respectively [9]. Also, 27,685,680 people have received the third dose of the COVID-19 vaccine, while the corresponding value for the second dose was 57,959,218 people [10].

Since the pandemic of COVID-19 and development of vaccines, permitting entry for travelers who have been completely vaccinated has become a common standard for countries across the world to prevent widespread transmission of the coronavirus. However, vaccination against the coronavirus disease and being vaccinated with a vaccine that a destination country (or WHO) accepts it as valid proof of immunity have turned out to be two separate issues. Accordingly, some countries may permit entry only to people who have been vaccinated with a number of COVID-19 vaccines such as the Pfizer-BioNTech, AstraZeneca, Moderna, and Johnson and Johnson vaccines which might be not available for all countries. In Iran, more than 130 million doses of COVID-19 vaccines have been used among the general population. However, the majority of such people received a vaccine that still has not been recognized by international institutions. In addition, some Iranian received vaccines that even have not been considered under EUL by WHO. This group encounters a problem to travel to countries that require a valid vaccine certificate.

In addition, with no full coverage of world population with vaccination against COVID-19, the pandemic is still far from extinction. The arrival of new variants that are most likely to be more transmissible and vaccine evasive as well as the pattern of waning of antibodies, the booster dosing of vaccine is highly recommended by WHO. However, such booster dose of vaccines, whether it is homologous or heterologous might be accompanied with adverse events.

Regarding the paucity of evidence on the adverse event of the booster dose of AstraZeneca vaccine in vaccinated people with Sinopharm and Sputnik V, we aim to set up a cohort event monitoring (CEM) study to capture adverse events occurring in individuals who will receive the booster vaccination with AstraZeneca (either the first or the second booster dose) following being vaccinated with Sinopharm or Sputnik V vaccines in Iran.

## Methods/design

### Objectives

#### General objective

Measuring safety of the booster doses of AstraZeneca vaccine in people vaccinated with two doses of Sinopharm or Sputnik V vaccines in Iran.

#### Specific objectives

To Estimate the incidence of different types of serious adverse events (SAEs) within 13 weeks in all enrolled vaccinated individuals after either the first or second booster vaccination with AstraZeneca.To estimate the incidence of different types of adverse events of special Interests (AESIs) within 13 weeks.To estimate the incidence of COVID-19 after either the first or second booster dose of A in all enrolled people.

### Design

The present study is an active COVID-19 vaccine safety surveillance through an observational prospective cohort study that will be conducted in vaccination centers in Iran. The present protocol has been developed based on the COVID-19 vaccine safety guidance manual introduced by the WHO in 2020 [11].

### Study settings

The study will be conducted in all major cities of Iran. Study sites are vaccination centers where the AstraZeneca is administered to the cohort population. Although vaccination against COVID-19 will be done in all health care centers plus other temporary locations, AstraZeneca has been provided in some predefined centers. In each site studied except Tehran, there will be a vaccination center to collect data on people get vaccinated by Astrazeneca. In Tehran, three vaccination centers have been determined to collect such data. Totally, we will collect data in all major cities. Study sites and vaccination centers will be selected by the Ministry of Health and Medical Education (MOHME). In order to receive the previous history of vaccination, we get access to Integrated Public Health System (IPHS). Table 1 shows characteristics of the cohort sites in the present study.

**Table 1 Tab1:** The main variables of the study gathered in enrolment and follow up questionnaires

Province	Site	Affiliation
Alborz	Alborz	Alborz University of Medical Sciences
Tehran	Tehran (TUMS)	Tehran University of Medical Sciences
Tehran	Tehran (SUMS)	Shahid Beheshti University of Medical Sciences
Tehran	Tehran (IUMS)	Iran University of Medical Sciences
Kermanshah	Kermanshah	Kermanshah University of Medical Sciences
Kurdistan	Sanandaj	Kurdistan University of Medical Sciences
Sistan and Baluchestan	Zahedan	Zahedan University of Medical Sciences
South Khorasan	Birjand	Birjand University of Medical Sciences
Kerman	Kerman	Kerman University of Medical Sciences
Razavi Khorasan	Mashhad	Mashhad University of Medical Sciences
Isfahan	Isfahan	Isfahan University of Medical Sciences
East Azerbaijan	Tabriz	Tabriz University of Medical Sciences
Khuzestan	Ahvaz	Ahvaz Jondishapur University of medical Sciences
Boshehr	Boshehr	Boshehr University of Medical Sciences

### Study period

The time point for enrolment will be either the first or second booster vaccination with AstraZeneca in one of the study sites, after primary vaccination with Sinopharm or Sputnik V.

Each individual will be followed-up for 13 weeks after either the first or second booster vaccination with AstraZeneca vaccine. Thirteen weeks follow-up period was chosen because this covers the most common risk windows for AESIs (42 days).

### Participants

The study population includes all enrolled individuals who have received two doses of Sinopharm vaccine and either the first or second booster dose of AstraZeneca according to the national guidelines for immunization against COVID-19 in Iran in 2023. In addition, those who have been vaccinated with two doses of Sputnik V and received the first or second dose of AstraZeneca recruited. Study participation is strictly voluntary, and signed informed consent is obtained from all participants. The process of including participants in the present cohort study is shown in Fig. 1.

**Fig. 1 Fig1:**
[figure not shown]
The flow chart of including participants in the present cohort study

#### Inclusion criteria

Written informed consent.Willingness to continue to participate in the study until 3 months.Enrolled individuals who have received the primary vaccination with two doses of Sinopharm or Sputnik V and either the first or second booster vaccination with AstraZeneca vaccine.

#### Exclusion criteria

Individuals unable to comply with study procedures (e.g. People with intellectual disabilities).Individuals who have received booster vaccination by AstraZeneca neither as the first nor as the second booster vaccination.Those who are less than 18 years old.

### Sample size estimation

Regarding the WHO’s protocol, the sample size required to rule out an event with a frequency of 1 per 3,333 with a 95% confidence interval is 10,000 per vaccine [11]. Therefore, we are planning to include 20,000 and 10,000 eligible people with previous vaccination with Sinopharm and Sputnik V respectively. Regarding the higher proportion of immunization coverage for the Sinopharm vaccine compared to Sputnik V in Iran, we will include more vaccinated people with the Sinopharm vaccine in the present study. Participants will be considered to have completed the study when they have completed the last questionnaire 13 weeks after the booster dose. The end of the study is defined as the point at which the last subject enrolled has reached the 3 months follow-up period. In this study, convenience sampling will be used to include eligible participants until achieving the required sample size.

### Subject recruitment and follow up

People who approach to one of the vaccination centers for booster vaccination, if they are eligible to be included, they will be consulted and get informed about the project. If they accept to participate, they will be asked to sign the consent form. On a day of vaccination, all the required information will be recorded on a web-based questionnaire. For weekly follow up, the study staff will call the participant by phone to collect data if the participant do not use the web application for self-reporting of adverse event. After two unsuccessful attempts to contact the participant by telephone, their next of kin will be contacted. After two unsuccessful attempts to contact their next of kin, the participant will be considered lost to follow-up if they do not complete the questionnaire by self-report. In fact, the participants are able to provide self-reported answers to all web-based questions using the mobile phone or a computer. The attempts to contact will be documented. We will record the underlying reason for withdrawal. Withdrawn participants and those lost to follow-up will not be replaced after the enrolment period has ended.

To identify SAEs and AESIs, each individual will be followed-up for 13 weeks after the booster dose of the AstraZeneca vaccine. The diagnoses reported by the participants during follow-up will be examined by a scientific committee including specialists in the field of infectious diseases, epidemiology, virology/immunology, internal diseases and others if needed. Such committees have been established by each university and they are involving in confirming the diagnosis for all SAEs and AESIs. In addition, there is a national committee to investigate adverse events related to vaccines, and therefore for all SAEs and AESIs, the patients’ files will be discussed in such committee. Such investigation helps participants to be treated within a standard protocol under the supervision of a scientific group.

As per WHO recommendation, all pregnant women inadvertently exposed to COVID-19 vaccine will follow up monthly until delivery, and the pregnancy outcome will be documented if it is possible. Although the available evidence does not fully support the use of AstraZeneca among pregnant women, we do not exclude such participants if they oblige to get a booster vaccination with AstraZeneca. The following maternal AESIs will be investigated among pregnant women: Maternal death and hospitalization, maternal thrombotic events, hypertensive disorders of pregnancy, miscarriage/spontaneous abortion, stillbirth, preterm birth, neonatal death, microcephaly, major congenital anomalies, infant death.

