### Study outcomes

#### Serious adverse events (SAEs): hospitalization, death

Serious adverse events (SAEs) is defined as any over-night hospitalization or death. SAEs that lead to in-patient hospitalizations will be reported by the participant or their next of kin, and SAEs that results in death will be reported by their next of kin [12].

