### Statistical analysis

In the present study, the data on SAEs and AESIs will be included for the whole cohort population. People who do not report any event(s) will be considered as participants without event(s). As AESIs can occur even after 42 days following the first booster dose, the sensitivity analysis will be done excluding those AESIs occurring within the first 12 days after the second booster dose.

We will calculate the frequency and proportion of participants reporting AESIs and SAEs by time since vaccination. For the proportions, 95% confidence intervals will be calculated using an exact method.Observed-to-expected analyses will be conducted for SAEs and AESIs with an unknown risk window (most likely situation). The observed incidences for AESIs will be compared with background rates from the most appropriate sources. The expected rate will be age-stratified, and the standardized incidence ratio (SIR) will be calculated.Incidence rate of severe COVID-19 disease (any COVID-19 disease diagnosed by a healthcare professional, laboratory-confirmed COVID-19, hospitalization for COVID-19, COVID-19 requiring intensive care unit (ICU) admission, COVID-19 disease resulting in death) will be calculated after either the first or the second booster dose of the AstraZeneca and within the period of follow-up.

The present study will be performed in line with the international ethical guidelines for epidemiology studies published by the Council for International Organizations of Medical Sciences (CIOMS), the Declaration of Helsinki and its amendments, good epidemiological practice (GEP) guidelines and the Iran National Committee for Ethics in Biomedical Research. Data protection and privacy regulations will be strictly observed in capturing, forwarding, processing, and storing individuals’ data. The study protocol and informed consent forms will be reviewed and approved by the Iran National Committee for Ethics in Biomedical Research.

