The present study can provide a first estimate of the incidence of SEAs and AESI and will give first insights into the incidence of new cases of Covid-19 among the cohort population after heterologous booster vaccination with AstraZeneca vaccine. In addition, it will help to measure the break through infection after booster vaccination.

There are some challenges in the present study. In the last years, the response rates tend to be low in population-based studies considerably [31, 32]. A low response rate might affect the representativeness of the cohort population which might have an effect on the generalizability of the incidence of SEAs and AESI in the Iranian source population.

Regarding that each individual should be followed-up for 13 weeks after either the first or second booster dose of the AstraZeneca vaccine, some participants might be lost to follow up due to a serious outcome such as severe events, hospitalization, or death. Some participants might not tend to be followed up for such a long time of 13 weeks. Also, some individuals may fail to complete the electronic questionnaire weekly because of poor access to a smartphone or forgetfulness. For participants who do not complete the electronic questionnaire regularly, the cohort vaccinators will contact them and fill out the follow-up questionnaire.

One of the major concerns is related to the new coming information regarding the safety of the AstraZeneca and the side effects which might lead to the AstraZeneca refusal among the cohort population [33]. This may in turn decrease our chance to reach the predefined sample size of our study.

Currently, we face remarkable low coverage of third or/and fourth doses of COVID-19 vaccine among the general population in Iran. To date (June 21, 2022), 27,685,680 people have received the third dose of the COVID-19 vaccine, while the amount for the second dose is 57,959,218. Given the notable decreasing trend of the first and second booster doses of vaccination, we might achieve the study sample size (30,000 people) within a longer period of time.

In addition, we will not monitor reactogenicity for either the first or the second booster dose of the AstraZeneca vaccine. In the present study, we just aim to investigate the SAEs (hospitalization, death), AESIs that result in hospitalization, and severe COVID-19 disease.

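### The loss-to-follow-up rule sets no minimum number of missed weeks and no re-contact, so a hospitalization or death can itself lead to loss and then be counted as no event

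*Protocol article*

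**What the plan says.** The protocol article, under Subject recruitment and follow up, sets out a contact sequence within a weekly cycle:

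- Trigger: "For weekly follow up, the study staff will call the participant by phone to collect data if the participant do not use the web application".
- Participant: "After two unsuccessful attempts to contact the participant by telephone, their next of kin will be contacted".
- Next of kin and loss: once two attempts to reach the next of kin have also failed, "the participant will be considered lost to follow-up if they do not complete the questionnaire by self-report".
- Duration: "each individual will be followed-up for 13 weeks after the booster dose of the AstraZeneca vaccine".

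The section does not say how far apart the four attempts are, how many weekly rounds must fail, or whether calling resumes after a failed round. It adds that people lost are not replaced once enrolment has ended.

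Three other places bear on this. Study outcomes: "Serious adverse events (SAEs) is defined as any over-night hospitalization or death", with deaths reported by next of kin. Discussion: "some participants might be lost to follow up due to a serious outcome such as severe events, hospitalization, or death". Statistical analysis: "People who do not report any event(s) will be considered as participants without event(s". That last rule makes no exception for people lost to follow-up.

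**The concern.** The event being counted can produce the silence that ends follow-up. Someone in hospital may answer neither the phone nor the web form, and someone who has died cannot. The next of kin then becomes the only informant named in the contact sequence, with two attempts. If those fail and the participant is classed as lost, the event is not recorded. Under the Statistical analysis rule the person nevertheless stays in the denominator as someone without an event.

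This pushes SAE and AESI proportions, and the observed-to-expected ratios built on them, downward, which is the unsafe direction for a vaccine safety study. The exact confidence intervals would also be calculated as though every enrolled person had been observed for 13 weeks.

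**Working it through.** **1. The plan's own figure.** Sample size estimation gives 10,000 per vaccine to rule out an event of frequency 1 per 3,333 at 95% confidence. Rule of three: 3 × 3,333 = 9,999. Exact one-sided zero-event form: ln(0.05) / ln(1 − 1/3,333) = 9,983. The figure reproduces, on the premise that all 10,000 are fully observed.

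**2. Illustrative loss under the rule as written.** The article gives no contact-failure rate. Let q be an assumed weekly probability that a whole round fails (participant, next of kin and web), independent from week to week. If one failed round leads to loss, the proportion lost by week 13 is 1 − (1 − q)^13. The last column shows the same q if two consecutive failed rounds were required.

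| q per week | Lost by week 13 | Of 30,000 | Lost if two consecutive failures needed |
|---|---|---|---|
| 0.5% | 6.3% | 1,893 | 0.03% |
| 1% | 12.2% | 3,674 | 0.12% |
| 2% | 23.1% | 6,929 | 0.47% |
| 5% | 48.7% | 14,600 | 2.8% |

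For a given average q, independence puts the one-round column at the upper end. If failures cluster in the same people, fewer distinct people are lost.

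**3. What q = 2% does to the sample-size premise.** The share of the 13 weeks observed is [(1 − q) + (1 − q)² + … + (1 − q)^13] / 13 = 0.871.

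- Sputnik V (10,000 planned): person-time equivalent to about 8,706 people. The zero-event bound is 8,706 / 2.996, about 1 in 2,900. Counting completers only gives 10,000 × 0.769 = 7,690 and about 1 in 2,570, but that discards the weeks observed before loss.
- Sinopharm (20,000 planned): 20,000 × 0.769 = 15,380 completers. Even at q = 5%, 20,000 × 0.513 is about 10,270.

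**4. Outcome-related loss.** Steps 2 and 3 model loss unrelated to the outcome. For the bias itself, let s be an assumed share of true SAEs never recorded because the round after the event fails for both participant and next of kin. With zero observed events in 10,000, the bound is 1 per 10,000 × (1 − s) / 3. The chance of seeing at least one event of frequency 1/3,333 is 1 − (1 − (1 − s)/3,333)^10,000.

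| s | Bound | Chance of at least one event | Share missed after a second, independent round (s²) |
|---|---|---|---|
| 0 | 1 per 3,333 | 95.0% | 0 |
| 10% | 1 per 3,000 | 93.3% | 1% |
| 20% | 1 per 2,667 | 90.9% | 4% |
| 30% | 1 per 2,333 | 87.8% | 9% |
| 50% | 1 per 1,667 | 77.7% | 25% |

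Neither q nor s can be estimated from the article. The tables show how the result responds to these values, not how large the bias is.

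**The case against.** The strongest reply is that the article does not say that one failed weekly round ends follow-up. It fixes neither the spacing of the four attempts nor the number of weeks, sets no deadline for web self-report, and does not forbid calling again. Call spacing is an operational detail that a condensed article may leave to the full protocol or to the planned data management plan. This stands in part: the single-round reading is an inference. It is still the natural one, because the article states a sequence inside a weekly cycle that ends in loss, and staff following it would have no instruction to resume.

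A reader might also infer that hospitalized or deceased participants are the ones cut off soonest. The document does not support that. Their silence triggers calls to the next of kin, who are named informants for hospitalization and the informants for death. Faster loss in this group would require next of kin to become harder to reach after an event, which is plausible but not documented. The next-of-kin step is real protection, though limited to two attempts.

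Other mitigating text goes only part of the way. The Discussion says staff will contact people who do not complete questionnaires regularly, but not what follows when those contacts fail. Source documents lists hospital and committee records, but under Subject recruitment and follow up the university committees examine diagnoses that participants report. The linkage described through the National code retrieves vaccination history. None of this clearly detects an event in a silent participant.

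Finally, the downward bias needs the event-free rule as well as the loss rule. That is correct; the two act together.

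**Conclusion.** The point holds in a limited form. As written, the contact rule allows loss to be declared with no minimum number of missed weeks and no re-contact. The outcomes can cause that failure, and the analysis rule then turns missing information into absence of an event. SAE and AESI incidence can therefore be biased downward, by an amount that the document does not allow anyone to compute.

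The 6% to 49% loss range rests on assumed weekly failure rates of 0.5% to 5%, independence between weeks and the single-round reading; it is illustrative and upper-end for each rate. At 2%, the Sputnik V zero-event bound moves from 1 in 3,333 to about 1 in 2,900. A reader might infer that the 10,000 target is undermined for both priming vaccines. It is not: Sinopharm plans 20,000 and keeps more than 10,000 completers across the whole assumed range.

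**What to change.** Amend Subject recruitment and follow up so that:

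- a failed round marks only that week as missed;
- calls resume at the next weekly round;
- a last attempt at week 13 asks the participant or next of kin about the whole interval since the last successful contact;
- the status of lost is assigned only if that attempt fails, and is dated at the last successful contact.

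Amend the event-free rule under Statistical analysis so that it applies only to observed time, and time after the last contact is not counted as event-free.

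The cost is some additional calls by existing staff within the existing weekly schedule, and one changed status rule in the web form. If resuming calls is already intended, one sentence saying so settles that part.

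### Pregnancy contact stops at delivery and pregnancies get no end-of-study exception, so the listed neonatal and infant deaths are only partly observed and their rates are biased low

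*Protocol article*

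**What the plan says.** Under Subject recruitment and follow up, the Protocol article keeps pregnant women in the cohort ("we do not exclude such participants if they oblige to get a booster vaccination with AstraZeneca") and gives them their own schedule: "all pregnant women inadvertently exposed to COVID-19 vaccine will follow up monthly until delivery". It adds that "the pregnancy outcome will be documented if it is possible". The list of maternal AESIs to be investigated closes with "stillbirth, preterm birth, neonatal death, microcephaly, major congenital anomalies, infant death". The same section states the general rule that "each individual will be followed-up for 13 weeks after the booster dose of the AstraZeneca vaccine", with weekly contact and no exemption for women who have delivered.

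Sample size estimation sets two end points. For the individual: "Participants will be considered to have completed the study when they have completed the last questionnaire 13 weeks after the booster dose". For the study: "The end of the study is defined as the point at which the last subject enrolled has reached the 3 months follow-up period". Inclusion criteria ask for "Willingness to continue to participate in the study until 3 months". None of the three mentions pregnancy.

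Statistical analysis takes SAE and AESI data over the whole cohort and treats anyone who reports no event as having had none.

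**The concern.** Three parts of the plan do not fit together.

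- Neonatal and infant death happen after birth, but the pregnancy-specific contact ends at birth.
- Contact up to delivery can itself run past the 13-week completion point and past the end of the study.
- The non-report rule turns missing observation into absence of an event. It reaches these outcomes because the plan labels them AESIs.

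The result would be pregnancy-outcome rates that are too low, in a group for which the protocol says the available evidence does not fully support use of the vaccine. The results go to the regulator and the immunization programme, where a low rate could be read as reassurance.

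**Working it through.** The plan gives no calculated figure for pregnancies. Its one design figure, 10,000 per vaccine for an event of 1 per 3,333, reproduces: 3/10,000 = 1/3,333, and exactly ln(0.05)/ln(1 − 1/3,333) = 9,983.3, rounded up to 9,984. Nothing below affects it. The check here is one of time windows.

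**Inputs from the article:** general follow-up W = 13 weeks after the booster; pregnancy contact to delivery; study end 3 months (taken as 13 weeks) after the last enrolment.

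**Assumptions not in the article:** term T = 40 weeks; neonatal period 28 days (4 weeks); infancy 52 weeks; gestational age at booster, g, spread evenly over a stated range.

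**1. Pregnancy-specific schedule alone.** Scheduled observation after delivery is 0 days, against 28 days and 52 weeks.

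**2. With the general 13-week follow-up.** Delivery comes T − g weeks after the booster, so the time left after delivery is P = max(0, 13 − (40 − g)) = max(0, g − 27).
- P is above 0 only if g exceeds 27 weeks.
- P reaches 4 weeks only if g is at least 31 weeks.
- The largest P is 13 weeks (g = 40), which is 13/52 = 25% of infancy.

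**3. Average coverage.** For an even spread over 0–40 weeks:
- delivered within 13 weeks: 13/40 = 32.5%
- full 28 days covered: 9/40 = 22.5%
- neonatal time covered: (½ × 4 × 4 + 9 × 4)/(4 × 40) = 44/160 = 27.5%
- infant-year time covered: (½ × 13²)/(52 × 40) = 84.5/2,080 = 4.1%

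| Gestation at booster (weeks) | Delivered within 13 weeks | Full 28 days | Neonatal time | Infant-year time |
|---|---|---|---|---|
| 0–14 | 0% | 0% | 0% | 0% |
| 0–40 | 32.5% | 22.5% | 27.5% | 4.1% |
| 14–40 | 13/26 = 50% | 9/26 = 34.6% | 44/104 = 42.3% | 84.5/1,352 = 6.25% |

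These are shares of time, not of deaths. The article says nothing on when deaths fall within these periods, so I do not convert them. They also assume that the weekly contact asks about the infant. Table 2, which lists only the main variables, shows pregnancy and abortion among the follow-up items but no birth or infant outcome.

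**4. Can contact to delivery be completed?** If the last enrolment comes k weeks after a woman's own booster, the study ends k + 13 weeks after that booster. She is undelivered at that point if 40 − g > k + 13, that is, if g < 27 − k.
- For the last woman enrolled (k = 0), this means any booster before about 27 weeks.
- At k = 27 or more, no woman is affected.
- Extreme case: enrolled last at 6 weeks, she has 40 − 6 = 34 weeks to go, and 34 − 13 = 21 of them (21/34 = 62%) fall after study end.

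The individual completion rule is wider. Read literally, it closes participation before delivery for every woman boosted before 27 weeks, whenever she was enrolled.

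**5. Direction of the error.** If a fraction c of the deaths falls in observed time and every pregnancy stays in the denominator as event-free, the reported proportion is c times the true one. Since c is below 1 whenever unobserved time carries risk, the error runs downwards only.

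**The case against.** A reader might infer that neonatal and infant deaths cannot be observed at all and will be reported as zero. The documents do not support that. The 13-week follow-up applies to every individual and runs past delivery for boosters from about 27 weeks. A death at or close to delivery may also be recorded as the pregnancy outcome.

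Nor does it follow that few late-pregnancy events will be seen. Stillbirth, preterm birth and hypertensive disorders fall mainly at or before delivery, and the study end cuts contact short only for women enrolled towards the close of recruitment. The Discussion expects recruitment may take longer than planned, so many women may deliver before the end. The 62% is a worst case for one woman and does not describe the pregnant cohort.

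Three further limits stand.
- The 3-month willingness item is an eligibility criterion. The consent form is not shown, so no consented duration can be asserted.
- Many congenital anomalies and cases of microcephaly are recognised at birth, so they do not belong with the deaths.
- Pregnancy outcomes are in neither the specific objectives nor the study outcomes, and they do not drive the sample size.

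It can also be said that the non-report rule never names pregnancy outcomes, and that recording the outcome only where possible admits gaps. This carries less weight. The article calls these outcomes AESIs, the rule covers AESIs in the whole cohort, and admitting gaps does not say how they are counted. The fact that the article is condensed does not answer the point either, because the conflict is between statements it does make.

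**Conclusion.** The point holds as a conflict between stated rules with a known direction of bias. Neonatal death is only partly observed: about 27.5% of neonatal time with gestation at booster spread over 0–40 weeks, ranging from 0% (0–14 weeks) to about 42% (14–40 weeks). Infant death is almost unobserved: about 4% of infant-year time, range 0% to about 6%, and never the full year. Completion of contact to delivery is not assured for early pregnancies enrolled late. With non-reporters counted as event-free, the rates are biased low by an amount the documents do not allow to be fixed.

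This rests on a 40-week term and an even spread of gestation; each week of earlier delivery moves the 27- and 31-week thresholds one week earlier. It also rests on reading the non-report rule as covering everything the plan calls an AESI. There is no consequence for sample size or for the main objectives.

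**What to change.** Reconcile Inclusion criteria, Sample size estimation, Subject recruitment and follow up, and Statistical analysis:

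1. Exempt pregnancies from the 13-week completion rule and the 3-month end of study, so that the promised contact to delivery is completed, and align the willingness criterion with it.
2. Either remove infant death, and neonatal death beyond the delivery contact, from the list, or define a post-delivery observation contact that supports them. One contact at about 28 days after birth would serve neonatal death; it is optional and would still not support infant death over the full year.
3. Exempt pregnancy outcomes from the non-report rule. Count undelivered or uncontacted pregnancies and infants as unknown, and use those actually observed as the denominator.

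The cost is amended wording, a supplementary pregnancy report after the main one and, if the post-delivery contact is chosen, one more phone call for what should be a small number of women.
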